### Mobile App and Baseline Assessments

A study-specific mobile app will be installed on participants’ smartphones and used as the central platform for remote monitoring. The app allows daily recording of physiological data, including heart rate (HR), peripheral oxygen saturation (SpO_2_), and oxygen flow rate. In addition, validated questionnaires (EQ-5D-5L, modified Medical Research Council [mMRC] Dyspnea Scale, Hospital Anxiety and Depression Scale [HADS], and COPD Assessment Test [CAT] or King Brief Interstitial Lung Disease [K-BILD] questionnaire, depending on diagnosis) will be self-administered through the app at predefined time points during follow-up. At baseline, all participants will complete the same standardized questionnaires through the app prior to randomization.

All participants will receive standardized training on the use of the pulse oximeter and the mobile app, as well as a written instruction manual. Participants in the intervention group (IG) will also receive detailed guidance on synchronizing the wearable device with the smartphone app.

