### Randomization and Blinding

Participants will be randomized in a 1:1 ratio to either the control group (CG) or the IG. The randomization sequence will be generated using an online randomizer (Sealed Envelope; Sealed Envelope Ltd) by an investigator who is not involved in patient recruitment, assessment, or intervention and who will perform the group allocation. Group allocation will be concealed using consecutively numbered, sealed, opaque envelopes. Randomization will be stratified by diagnosis (ILD or COPD).

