### Statistical Analysis

The sample size calculation, based on the primary outcome of the study (EQ-5D-5L), was informed by a previous study reporting an observed difference of 0.04 in the EQ-5D-5L index, which was considered clinically meaningful within that specific study population [13]. This value was used as a pragmatic estimate of the expected effect size for sample size determination. The calculation was performed using G*Power software (*F* tests: ANOVA, repeated measures, within-between interaction). The calculation assumed an effect size of *f*=0.25, a 2-sided α level of .05, and a statistical power of 90% (β=.10). The design included 2 groups and 4 repeated measurements, with a correlation among repeated measures of 0.5 and a nonsphericity correction (ε) of 0.5. On the basis of these assumptions, the required sample size was 50 participants (25 per group), with an achieved power of 0.91. Considering an anticipated dropout rate of 20%, the final target sample size was increased to 30 participants per group to preserve statistical power under an intention-to-treat framework. The significance level will be set at 5% (*P*<.05) for all statistical tests, which will be conducted using GraphPad Prism (version 5.0; GraphPad Software LLC).

Data normality will be assessed using the Kolmogorov-Smirnov test, and homoscedasticity will be evaluated using the Levene test. Parametric data, defined by a normal distribution as demonstrated by histograms, will be presented as means and SDs (or SEs), while nonparametric variables will be presented as medians and IQRs.

Longitudinal outcomes will be analyzed using linear mixed-effects models with fixed effects for group, time, and group-by-time interaction and random intercepts for participants. The results will be interpreted in light of the established MCIDs for each outcome measure. Additionally, as a complementary analysis, the proportion of participants in each group achieving a within-individual change equal to or greater than the MCID will be calculated, providing a more clinically meaningful interpretation of the findings. Sensitivity analyses will be conducted to assess the robustness of the results.

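### The longitudinal model lets the arms differ at a baseline taken before randomization, which wastes precision; fix a common baseline (or adjust for it), add diagnosis, and name one primary contrast

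*Protocol article*

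**What the plan says.** All references are to the protocol article.

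- **Model (Statistical Analysis).** "Longitudinal outcomes will be analyzed using linear mixed-effects models with fixed effects for group, time, and group-by-time interaction", plus random intercepts. No baseline covariate, baseline constraint or diagnosis term is listed.
- **Number of measurements (Statistical Analysis).** "The design included 2 groups and 4 repeated measurements, with a correlation among repeated measures of 0.5 and a nonsphericity correction (ε) of 0.5". Table 1 and the Interventions section place the EQ-5D-5L at baseline and days 30, 60 and 90, so baseline is one of the four.
- **Timing of baseline (Mobile App and Baseline Assessments).** "At baseline, all participants will complete the same standardized questionnaires through the app prior to randomization".
- **Stratification (Randomization and Blinding).** "Randomization will be stratified by diagnosis (ILD or COPD").
- **Sizing (Statistical Analysis).** "The calculation was performed using G*Power software (*F* tests: ANOVA, repeated measures, within-between interaction"), giving the result that "the required sample size was 50 participants (25 per group), with an achieved power of 0.91".
- **Primary outcome (Outcomes).** The EQ-5D-5L is described with both an index and a visual analog scale (VAS). The sizing refers to the index. No visit or contrast is named as the one that decides the primary question.
- **Status (Results).** 62 participants were randomized, 60 entered the longitudinal analysis and 49 completed 90 days. Data collection is finished and analysis is under way.

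**The concern.** When baseline is an outcome row and the model has a free group effect, each arm gets its own baseline mean. The day-90 group difference, taken relative to baseline, is then a difference in change scores. Because baseline precedes randomization, the model is estimating a baseline difference whose true value is zero, and the noise in that estimate carries into every later contrast.

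Nothing becomes biased. What is lost is precision, in a trial of 60 people that can no longer recruit. The model also leaves out the factor used to stratify the randomization, and the text does not single out one comparison on which the primary conclusion will rest.

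**Working it through.** **1. The plan's own figure.** Inputs from Statistical Analysis: f = 0.25, N = 50, m = 4 measurements, k = 2 groups, ρ = 0.5, ε = 0.5, α = 0.05.

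- λ = f²·N·m·ε/(1−ρ) = 0.0625 × 50 × 4 × 0.5/0.5 = 12.5
- df1 = (k−1)(m−1)ε = 1.5; df2 = (N−k)(m−1)ε = 72
- Power = 0.909, against 0.91 stated. The figure reproduces.
- With N = 49 the same formula gives 0.903.

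**2. Day-90 contrast.** Take a common variance σ², correlation ρ between any two visits (what a random intercept implies), complete data and categorical visits. In units of 2σ²/n, with n per arm:

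- Free baseline means (as written): 2(1−ρ) = 2 × 0.5 = 1.00
- Common baseline mean: 1−ρ² = 1 − 0.25 = 0.75
- Proportional saving: 1 − (1−ρ²)/[2(1−ρ)] = (1−ρ)/2, which is positive for any ρ below 1

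| ρ | Free | Common | Saving |
|---|---|---|---|
| 0.3 (assumed) | 1.40 | 0.91 | 35% |
| 0.5 (plan) | 1.00 | 0.75 | 25% |
| 0.7 (assumed) | 0.60 | 0.51 | 15% |
| 0.8 (assumed) | 0.40 | 0.36 | 10% |

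At ρ = 0.5 the free-baseline model needs 50/0.75 ≈ 67 participants to match 50 under the constrained model.

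**3. Average of days 30, 60 and 90, at ρ = 0.5.** The mean of three visits has variance (1+2ρ)/3 = 0.667 and covariance ρ = 0.5 with baseline.

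- Free: 0.667 + 1 − 2 × 0.5 = 0.667
- Common: 0.667 − 0.5² = 0.417
- Saving: 37.5%

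**4. Diagnosis.** Assume that diagnosis explains a share R of total variance as a stable between-person difference. Given diagnosis, the variance is 1−R and the covariance between visits is 0.5−R.

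- Model as written: 2[(1−R) − (0.5−R)] = 1.00 for any R. There is no gain, because the random intercept already absorbs diagnosis.
- Common baseline: (1−R) − (0.5−R)²/(1−R). For R = 0.05 this is 0.737 and for R = 0.10 it is 0.722, against 0.75 without diagnosis. The further saving is about 2% and 4%.

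**5. Which contrast?** The table gives the power of a single-degree-of-freedom test with 25 per arm and ρ = 0.5. Each effect is scaled so that a 3-df interaction test with free baselines would have power 0.90. The table serves only to rank the options and is not a power forecast.

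| Effect shape (assumed) | Day 90, free | Day 90, common | Average, free | Average, common |
|---|---|---|---|---|
| Constant from day 30 | 0.872 | 0.947 | 0.966 | 0.998 |
| Rising linearly to day 90 | 0.949 | 0.986 | 0.836 | 0.960 |
| Day 90 only | 0.872 | 0.947 | 0.244 | 0.359 |

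The common baseline helps in every row. Neither contrast wins in every row.

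**The case against.** The strongest reply has four parts.

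- **The stated model is valid.** It gives unbiased estimates, and the interaction-based sizing matches a group-by-time analysis. This is true, and it makes the point one of efficiency only.
- **The article is condensed, and covariates and contrasts are often left to an analysis plan.** That excuses silence on detail. It does not remove the baseline point, because the article lists the fixed effects and the listed set frees the baseline mean. That baseline is an outcome row follows from the count of four measurements and the assessment schedule; it is not said outright.
- **The gain depends on ρ.** This stands: 25% belongs to the plan's 0.5, and 10% is the figure if ρ is 0.8.
- **The shortfall in completers is slight.** This also stands. Under the plan's inputs, 49 instead of 50 moves power from 0.909 to 0.903, and the mixed model also uses partial data from the other 11 of the 60. The count shows that there is no slack; it does not show that the trial has failed.

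Some stronger readings are tempting, but the documents do not support them.

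- **That omitting diagnosis loses precision in the model as written.** Step 4 shows that it does not.
- **That the plan commits to a 3-df test.** That comes from the sizing calculation. The analysis text names no test and does not say whether time is categorical; with linear time the interaction has 1 df.
- **That a single-contrast test always beats the omnibus test.** With a constant effect, the free-baseline day-90 test has 0.872 against 0.90. Any one power comparison would need an effect size in SD units and a shape, and the documents do not supply both.
- **That the family-wise error is badly inflated.** That supposes free choice among the index, the VAS and the visits. The Statistical Analysis section labels group comparisons at specific time points exploratory, and the sizing refers to the index.

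**Conclusion.** The point holds as a matter of efficiency. As written, the model estimates a separate baseline mean in each arm although the true means are equal by design. At the plan's ρ of 0.5, a common baseline mean reduces the variance of the day-90 contrast by 25% and that of the post-baseline average by 37.5%. Over assumed ρ from 0.3 to 0.8 the day-90 saving runs from 35% to 10%.

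These figures assume compound symmetry, equal variances, complete data and categorical visits. With 49 of 60 completing, absolute precision will be lower than in the calculation. Neither bias nor an inflated type I error is shown.

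Diagnosis belongs in the model because the randomization was stratified by it; the expected extra gain is small. The choice of primary contrast should be made in advance, since its merit depends on an effect shape that nobody knows. The change is well worth making, but the stated analysis would not be invalid without it.

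**What to change.** Replace the model statement with one of the following:

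- a baseline-constrained longitudinal model: categorical visit, no group effect at baseline, group-by-visit terms at days 30, 60 and 90, and diagnosis; or
- a model of the three post-baseline visits with the baseline value as a covariate, plus group, visit, group-by-visit and diagnosis.

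Then name one primary single-degree-of-freedom contrast on the EQ-5D-5L index: either the group difference at day 90 or the group difference averaged over days 30, 60 and 90. The team should choose on the clinical question, noting that day 90 is the visit most exposed to dropout and that the average is weak if benefit appears only late. Make the VAS and the remaining visits secondary.

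The cost is analysis-plan wording and code; no new data are needed. Because analysis has started, the change must be dated and documented before results by arm are seen, with a statement of what had been seen by then. If the team regards it as an important modification, the Ethical Considerations section requires submission to the ethics committee and an update of the registry entry. If results by arm have already been viewed, report the stated model as planned and the constrained model as a sensitivity analysis.

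### The sample size allows for nonsphericity (ε = 0.5), but the stated random-intercept model does not, so the group-by-time test may run at up to about 9% instead of 5%

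*Protocol article*

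**What the plan says.** Both statements stand in the Statistical Analysis section of the protocol article.

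- **Sample size.** The G*Power test is "ANOVA, repeated measures, within-between interaction", with "an effect size of *f*=0.25" and "a 2-sided α level of .05". The section adds: "The design included 2 groups and 4 repeated measurements", "with a correlation among repeated measures of 0.5 and a nonsphericity correction (ε) of 0.5". The result is 50 participants with power 0.91, raised to 60 for dropout.
- **Analysis.** Longitudinal outcomes, which include the primary EQ-5D-5L, are to be analysed with "linear mixed-effects models with fixed effects for group, time, and group-by-time interaction and random intercepts for participants". The section names no random slope, residual covariance structure, robust standard error or ε correction. All tests are at 5%, and GraphPad Prism 5.0 is named as the software.

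Sensitivity analyses are promised twice, without content. The Results section reports 60 participants in the longitudinal analysis, 49 completers, and analysis still under way.

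**The concern.** A random intercept with independent residuals gives every visit the same variance and every pair of visits the same correlation. That is compound symmetry, for which ε is exactly 1. With four visits ε can range from 1/3 to 1, so the planning value of 0.5 is a marked departure.

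The plan thus budgets for nonsphericity and then names a test that assumes there is none. The affected test is the one on which the trial was powered, for the primary outcome. If the data behave as the sample size supposes, a benefit of remote monitoring would be declared by chance more often than the stated 5%.

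**Working it through.** **Inputs** (Statistical Analysis section): k = 2 groups, m = 4 visits, f = 0.25, ρ = 0.5, ε = 0.5, α = 0.05, N = 50.

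**1. Reproduce the plan's figure.** For the within-between interaction:
- λ = f²·N·m·ε/(1−ρ) = 0.0625 × 50 × 4 × 0.5/0.5 = 12.5
- df1 = (k−1)(m−1)ε = 3 × 0.5 = 1.5
- df2 = (N−k)(m−1)ε = 48 × 3 × 0.5 = 72
- Power from the noncentral F = 0.909. N = 48 gives 0.897, so 50 is the smallest even N that reaches 0.90. Both stated figures reproduce.

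**2. What ε contributed.** With ε = 1 and all else unchanged, N = 30 gives λ = 15, df = 3 and 84, and power 0.903. The ε value alone moved the requirement from 30 to 50.

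**3. True size of the interaction test.** On complete balanced data with a non-negative intercept variance estimate, the random-intercept interaction test equals the uncorrected repeated-measures F test on 3 and 3(N−2) df. At N = 50 its 5% critical value is F(3, 144) = 2.667. By Box's approximation the true size is P[F(3ε, 3(N−2)ε) > critical value]:

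| ε | N = 50 | N = 60 |
|---|---|---|
| 1.0 | 5.0% | 5.0% |
| 0.9 | 5.6% | 5.6% |
| 0.75 | 6.7% | 6.7% |
| 0.5 | 9.1% | 9.1% |
| 1/3 (lower bound) | 10.9% | 10.9% |

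Simulation with no true effect (40,000 trials per setting, N = 50 and 60):
- ε = 0.5 (random slope, or extra variance at baseline, day 30 or day 90): 8.4% to 8.7%.
- AR(1) correlations of 0.65, 0.70 and 0.80 (ε = 0.79, 0.77, 0.72), N = 50: 6.3%, 6.5% and 6.8%. Separate runs at 0.70 gave 6.1% to 6.2%.
- Compound symmetry, as a control: 4.8% to 4.9%.

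**4. Group main effect.** In the same simulations it rejects in 4.8% to 5.2% of trials. It is not inflated.

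**5. Day 90 minus baseline.** The model takes the variance of this within-person difference as twice the average within-person residual variance. The size depends on the ratio of true to assumed variance, R, and is roughly P(|Z| > 1.98/√R). Variances below are in units of the residual variance, or of the total variance for AR(1).

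| True covariance | True / assumed variance | R | Approximate size | Simulated size |
|---|---|---|---|---|
| Random slope, ε = 0.5 | 15.04 / 6.83 | 2.20 | 18.3% | 18.7% |
| Extra variance at baseline or day 90, ε = 0.5 | 11.66 / 6.83 | 1.71 | 13.0% | 13.3% to 13.6% |
| AR(1), 0.70 | 1.314 / 0.859 | 1.53 | 11.0% | 11.2% to 11.3% |
| Extra variance at day 30, ε = 0.5 | 2.00 / 6.83 | 0.29 | <0.1% | <0.1% |

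Over AR(1) correlations of 0.65 to 0.80 the approximation runs from 10.5% to 12.0%. The same ε of 0.5 can therefore make this contrast strongly anticonservative or strongly conservative, depending on where the extra variance lies.

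**The case against.** **The model may be incompletely described rather than wrong.** The article does not state that residuals are independent, and a fuller plan could add a structured residual or robust standard errors. This stands as a caveat. But the article does choose a covariance structure, and its ordinary reading is compound symmetry. The point sets that stated choice against a stated planning figure; it is not a complaint about missing detail.

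**ε = 0.5 may be mere caution.** Lowering ε in the calculation only raises N, and the same sentence gives a single correlation of 0.5, which with equal variances would mean ε = 1. This also stands: the inflation is conditional on ε, and near sphericity it is small.

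**Sensitivity analyses are promised.** They have no stated content and would not correct the primary P value.

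**Two stronger readings are not supported.**
- A reader might infer that every primary test exceeds 5%. The group main effect does not.
- A reader might infer that nearly one trial in five would give a false positive, from the 18.7% for day 90 minus baseline. The article never names that contrast as primary. The figure also needs a random slope so strong that the variance rises from 1.68 at baseline to 14.72 at day 90, an SD ratio of √8.75 ≈ 3.0 (2.7 if the intercept variance equals the residual variance). That is hard to expect over 90 days in clinically stable participants, and other covariances with the same ε reverse the direction.

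**Conclusion.** The mismatch is real and confined to terms that involve time. At the plan's own ε of 0.5, the nominal 5% group-by-time test has a type I error of about 8.5% to 9%. For milder departures (ε about 0.72 to 0.79) it is about 6% to 7%, and at ε = 0.9 it is 5.6%. Standard errors for single-visit contrasts can be wrong in either direction.

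These figures assume independent residuals around the random intercept and complete data at all four visits. With 49 of 60 participants completing, the exact values would shift, but the mechanism is the same. The documents do not show what ε is in these data. The plan should be corrected, but the size of the problem does not by itself invalidate the trial.

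**What to change.** Replace the random-intercept-only structure with an unstructured covariance over baseline and days 30, 60 and 90, and use Kenward-Roger degrees of freedom for the fixed effects. State in advance a fallback for non-convergence, for example a simpler structure such as heterogeneous Toeplitz or AR(1), with robust standard errors. Robust standard errors or an ε-corrected interaction test would also address the problem. Confirm that the named software can fit the chosen model, and name another package if it cannot. Record the choice before anyone sees between-group results, because the analysis is already under way.

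The cost is small. Four visits need 4 × 5/2 = 10 covariance parameters instead of 2, and intervals may be slightly wider. For this point the sample size needs no change, because the calculation already allows for ε = 0.5.

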**Methods:**

This randomized controlled trial will recruit 60 participants, including clinically stable adults diagnosed with chronic obstructive pulmonary disease (COPD) or interstitial lung disease (ILD) who use LTOT. Participants will be randomized in a 1:1 ratio to either the control group (CG) or the intervention group (IG), stratified by diagnosis (COPD or ILD), and will be followed for 90 days. All participants will use a mobile app that serves as the central platform for remote monitoring. The app enables daily recording of physiological data, including heart rate (HR), peripheral oxygen saturation (SpO_2_), and oxygen flow rate. In addition, validated questionnaires (EQ-5D-5L, modified Medical Research Council [mMRC] Dyspnea Scale, Hospital Anxiety and Depression Scale [HADS], and COPD Assessment Test [CAT] or the King Brief Interstitial Lung Disease [K-BILD] questionnaire, depending on diagnosis) will be self-administered through the app at predefined time points. The CG will receive monthly telephone follow-up (every 30 days), while the IG will receive biweekly telephone follow-up (every 15 days). During these structured calls, trained health care professionals will collect clinical information and ensure data completeness. In addition, participants in the IG will use a wearable smartwatch that enables continuous physiological monitoring (HR and SpO_2_), with data transmitted to a secure platform and analyzed weekly using an AI-assisted system to support adherence monitoring and identify physiological patterns. Participants in the IG may receive additional contact if clinically relevant abnormalities or reduced adherence are detected. Outcomes will be interpreted according to the minimal clinically important difference (MCID) for dyspnea (mMRC Dyspnea Scale), health status (CAT or K-BILD), quality of life (EQ-5D-5L), and psychological symptoms (HADS).

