## Methods

### Participants

Individuals of either sex aged 18 to 85 years with chronic hypoxemia due to chronic obstructive pulmonary disease (COPD) or interstitial lung disease (ILD) will be eligible if they have been receiving LTOT for at least 6 months, are receiving optimized pharmacological treatment, and have had no exacerbations during the preceding 2 months. They also need to own a smartphone compatible with the app that monitors quality of life and vital signs. Exclusion criteria will include cognitive or other limitations that impair the understanding of questionnaires, residence outside the metropolitan area where the hospital is located, and inability to use a smartphone or use of a device with an operating system other than iOS or Android. Participants will be screened and recruited at the pulmonology outpatient clinic of a tertiary university hospital. Enrollment in the study will occur after the informed consent form is signed. The schedule of enrollment, allocation, interventions, and assessments is outlined in Table 1.

**Table 1 table1:** Schedule of study assessments and data collection during the 90-day follow-up period.

Assessments	Screening	Baseline (day 0)	Day 15	Day 30	Day 45	Day 60	Day 75	Day 90
Eligibility screening	✓							
Informed consent	✓							
Randomization		✓						
Mobile app installation and training		✓						
Control group telephone follow-up				✓		✓		✓
Intervention group telephone follow-up			✓	✓	✓	✓	✓	✓
Wearable monitoring (intervention group)		✓	✓	✓	✓	✓	✓	✓
Daily physiological data entry via the mobile app^a^		✓	✓	✓	✓	✓	✓	✓
EQ-5D-5L		✓		✓		✓		✓
Hospital Anxiety and Depression Scale		✓		✓		✓		✓
Modified Medical Research Council Dyspnea Scale		✓		✓		✓		✓
COPD Assessment Test or King Brief Interstitial Lung Disease questionnaire		✓		✓		✓		✓

^a^Participants are instructed to enter physiological data into the mobile app daily throughout the follow-up period.

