### Interventions

#### Control Group

Participants in the CG will receive a pulse oximeter (Morya, model AS304) and will be followed for 90 days. They will receive monthly telephone follow-up every 30 days. During these structured calls, a trained health care professional will collect clinical information, including exacerbations, respiratory symptoms (cough, dyspnea, and shortness of breath), medication adherence, and oxygen use. All study questionnaires (EQ-5D-5L, mMRC Dyspnea Scale, HADS, and CAT or K-BILD, depending on diagnosis) will be self-administered by participants through the mobile app at predefined time points (baseline, day 30, day 60, and day 90). During scheduled telephone follow-up calls, health care professionals will reinforce questionnaire completion, collect clinical information (exacerbations, respiratory symptoms, medication adherence, and oxygen use), and provide support as needed. HR and SpO_2_ will also be recorded using the pulse oximeter on the day of follow-up. Participants will continue using the mobile app for daily recording of physiological data.

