##### Patient Adherence

Adherence will be assessed based on data entry into the mobile app. A participant will be considered adherent if data (HR, oxygen saturation, and oxygen flow) are entered for at least 30 of the 90 days of follow-up [23,24]. This threshold was defined to ensure a minimum level of engagement with the monitoring system while accounting for occasional missed entries.

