The adherence criterion will be used in exploratory subgroup analyses to compare outcomes between adherent and nonadherent participants [25]. All primary longitudinal analyses will follow a modified intention-to-treat approach, including randomized participants who initiated follow-up and contributed data to the longitudinal analysis, regardless of adherence status. This approach preserves the benefits of randomization and reflects real-world conditions. Sensitivity analyses will be conducted to assess the robustness of the results.

For exploratory purposes, when appropriate, comparisons between groups at specific time points may be performed using parametric or nonparametric tests (eg, the *t* test or Mann-Whitney test), depending on data distribution. Pearson correlation coefficients will be used to assess associations between normally distributed variables, while Spearman correlation coefficients will be used for nonnormally distributed variables.

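### The exploratory adherent-versus-nonadherent comparison groups participants by behaviour during the outcome period, so it can show a difference when data entry has no effect

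*Protocol article*

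**What the plan says.** The Patient Adherence subsection counts a participant as adherent if heart rate, saturation and oxygen flow "are entered for at least 30 of the 90 days of follow-up". A footnote to Table 1 sets the instruction behind this: "Participants are instructed to enter physiological data into the mobile app daily throughout the follow-up period". Table 1 places the questionnaires at baseline and days 30, 60 and 90, inside the window in which entries are counted.

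The Statistical Analysis section then applies this definition, in subgroup analyses labelled exploratory, "to compare outcomes between adherent and nonadherent participants". It attaches no early classification window, lag, adjustment or caution about interpretation to that comparison. The same paragraph protects the main result: "All primary longitudinal analyses will follow a modified intention-to-treat approach", applied "regardless of adherence status".

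The arms differ in how strongly entry is encouraged. The Abstract says: "Participants in the IG may receive additional contact if clinically relevant abnormalities or reduced adherence are detected". The Intervention Group subsection makes two consecutive days without entry an alert criterion. Table 1 schedules six calls in the intervention group (days 15, 30, 45, 60, 75 and 90) and three in the control group (days 30, 60 and 90). The Discussion accepts that this difference may affect adherence.

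**The concern.** Adherence here is a result of what happens during follow-up. Three things can separate the two groups without any effect of data entry:

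- **Reverse causation and confounding by health.** A participant who deteriorates may stop entering data and also report a worse score. The score is then poor in the nonadherent group because poor health put the participant there.
- **Mixing with arm.** Low-adherence contacts and twice as many calls can raise entry in the intervention group. A pooled comparison by adherence then carries part of any arm effect.
- **Guaranteed time.** Nobody can collect 30 entry days before about day 30. Early leavers are therefore always nonadherent, and any day-30 outcome would be grouped partly by later behaviour.

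At stake is a secondary message: the paper could report that participants who engaged with the app did better when the data show only that healthier participants engaged.

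**Working it through.** The plan gives no figure for this comparison, so there is none to reproduce. The benchmark is the 0.04 index difference in the sample size paragraph.

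**Inputs from the article.** 60 participants analysed and 49 completed, so 60 − 49 = 11 did not complete, 11/60 = 18.3%. Adherent means at least 30 of 90 days.

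**Assumptions, not in the article.** SD 0.20 for the index; median daily entry probability 0.35 or 0.50, with person-to-person variation of SD 1 on the logit scale; dropout day uniform over days 1 to 90. The log-odds of entry change by b per SD of health change. At a median of 0.50, b = 0.5 means that a participant 1 SD worse enters with probability 1/(1 + e^0.5) = 0.38. The true effect of entry on outcome is zero throughout.

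**Step 1: health change drives entry.** Change to day 90 is compared between adherent and nonadherent completers, counting |t| > 2.0 as a false positive. The ranges cover all scenarios run (1,000 to 1,500 trials each), including some with dropout related to health.

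| b | Spurious difference (index) | False positives |
|---|---|---|
| 0 | about 0.00 | 4–7% |
| 0.5 | 0.07–0.08 | 22–27% |
| 1 | 0.13–0.15 | 62–72% |
| 2 | 0.21–0.23 | 97–100% |

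At b = 0.5 this is 0.07/0.04 = 1.75 to 0.08/0.04 = 2 times the benchmark. In index points the differences scale with the assumed SD.

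**Step 2: guaranteed time alone.** With dropout unrelated to health, 7–8% of adherent participants are dropouts, against 28–40% of nonadherent participants. No participant who left by day 30 was ever classed adherent. Among completers with b = 0, this alone produced no bias in the score.

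**Step 3: early classification.** Adherence is now at least 10 entries in days 1 to 30 (10/30 = 30/90, the same one-third rate), and the outcome is change from day 30 to day 90, median entry probability 0.50.

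| b | As planned | Landmark, independent health increments | Landmark, straight-line decline |
|---|---|---|---|
| 0.5 | 0.077–0.081 | −0.002 (6.0% false positives) | 0.017 (8.5%) |
| 1 | 0.145–0.148 | 0.002 (6.7%) | 0.036 (14.5%) |
| 2 | 0.208–0.226 | 0.002 (6.0%) | 0.066 (33.9%) |

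With regression adjustment at b = 0.5, the baseline-adjusted 30-of-90 comparison is still biased by about 0.075. A day-30 landmark adjusted for baseline and day-30 score brings this to about 0.01–0.02.

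**Step 4: stable health level drives entry.** If one fixed health factor drives both score and entry, b = 0.5 gives about 0.104 on raw day-90 scores but only 0.001–0.002 on change from baseline. The landmark alone still leaves about 0.10 on raw scores. With baseline adjustment the landmark leaves 0.054 and the 30-of-90 grouping 0.056. In this setting the gain comes from using baseline, not from the earlier window.

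**The case against.** The strongest reply is that the plan already limits the damage. The comparison is labelled exploratory, the primary analyses ignore adherence status, and the Discussion concedes that follow-up intensity may affect adherence. The covariates and visits of an exploratory analysis may also be left to a fuller document. The article does not say that raw scores are compared, or that day-30 scores enter this comparison. Where only a stable health level drives entry, analysing change from baseline removes the bias.

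Most of this stands and limits the weight of the point. It does not remove it. The grouping and its window are stated choices, and when health change drives entry, neither change scores nor baseline adjustment corrects the comparison.

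A reader might go further, and the documents do not support that:

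- **Immortal-time bias in the strict sense.** That concerns survival-type outcomes. Here the outcomes are scale scores at fixed visits, and Step 2 shows no score bias among completers from the time element alone.
- **A large false benefit as a certainty.** The size depends on an unknown link and is nil without one.
- **A planned causal claim about app entry.** The Discussion's remark on engagement concerns the study hypothesis, which is the randomized contrast. Its remark on adherence to therapy concerns oxygen use.
- **Randomization as an instrument for entry.** The intervention group also receives a watch, more calls and physiological alerts, so arm can affect outcomes by other routes.

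**Conclusion.** The point holds as a limited one. As stated, the adherent-versus-nonadherent comparison rests on a post-randomization grouping that shares its window with the outcomes and is partly driven by arm. It can give a difference of about 0.07–0.08 index points with no true effect if the link between health change and entry is moderate (b = 0.5) and the SD is 0.20. With no link it gives none. Both inputs are assumptions. The article also does not say when the 11 non-completers left, so the number made nonadherent by early departure is unknown. The primary modified intention-to-treat comparison is not touched. The change is worth making before this analysis is run; the Results section says analysis is still ongoing.

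**What to change.** Replace the comparison in the Statistical Analysis section with a day-30 landmark analysis:

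1. Classify participants by entries in days 1 to 30, for example at least 10 of 30.
2. Include only those still followed at day 30.
3. Compare day-60 and day-90 outcomes, adjusting for arm, diagnosis, baseline score and day-30 score. The landmark without these adjustments is not enough (Step 4).
4. Report the result as association only, because residual confounding remains.

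Keep the 30-of-90 definition for the descriptive adherence outcome. Do not add an instrumental-variable estimate.

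The cost is a few sentences and a short piece of analysis code; the daily entries have already been collected. The small downside is that participants lost before day 30 leave this exploratory analysis.
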